## Abstract

**Background:**

The National Institute for Health Research (NIHR) has funded nine Collaborations for Leadership in Applied Health Research and Care (CLAHRCs). Each CLAHRC is a partnership between higher education institutions (HEIs) and the NHS in nine UK regional health economies. The CLAHRC for Leeds, York, and Bradford comprises two 'research themes' and three 'implementation themes.' One of these implementation themes is Translating Research into Practice in Leeds and Bradford (TRiPLaB). TRiPLaB aims to develop, implement, and evaluate methods for inducing and sustaining the uptake of research knowledge into practice in order to improve the quality of health services for the people of Leeds and Bradford.

**Methods:**

TRiPLaB is built around a three-stage, sequential, approach using separate, longitudinal case studies conducted with collaborating NHS organisations, TRiPLaB will select robust innovations to implement, conduct a theory-informed exploration of the local context using a variety of data collection and analytic methods, and synthesise the information collected to identify the key factors influencing the uptake and adoption of targeted innovations. This synthesis will inform the development of tailored, multifaceted, interventions designed to increase the translation of research findings into practice. Mixed research methods, including time series analysis, quasi-experimental comparison, and qualitative process evaluation, will be used to evaluate the impact of the implementation strategies deployed.

**Conclusion:**

TRiPLaB is a theory-informed, systematic, mixed methods approach to developing and evaluating tailored implementation strategies aimed at increasing the translation of research-based findings into practice in one UK health economy. Through active collaboration with its local NHS, TRiPLaB aims to improve the quality of health services for the people of Leeds and Bradford and to contribute to research knowledge regarding the interaction between context and adoption behaviour in health services.

## Background

In response to the recommendation of the Chief Medical Officer's Clinical Effectiveness Group that the NHS should better utilise higher education to support initiatives to enhance the effectiveness and efficiency of clinical care [1], the National Institute for Health Research (NIHR) announced a strategy of increasing partnerships between higher education and the NHS in local health economies. One means of developing these partnerships is Collaborations in Leadership and Applied Health Research and Care or CLAHRCs. The NIHR has funded nine CLAHRCs, each with an emphasis on research that makes an impact locally and with a strong, disciplined, and strategic approach to implementing that research. The NIHR CLAHRC for Leeds, York and Bradford (LYBRA) comprises two 'research' programmes (Improving Vascular Prevention in Cardiac and Stroke Care (IMPROVE-PC), Improving the Quantity and Quality of Life in People with Addictions) and three 'implementation' programmes (Outcome Driven Stroke Care, Maternal and Child Health, and the focus of this protocol, Translating Research into Practice in Leeds and Bradford, or TRiPLaB).

The aim of TRiPLaB is to develop, implement, and evaluate methods of inducing and sustaining the uptake of research into practice in order to improve the quality of health services for the people of Leeds and Bradford. Research implementation is a complex process, highly dependent on context, and interactions between multiple, interconnected, factors at the level of individuals, groups, organisations and wider health systems [2-6]. Despite this complexity, or perhaps because of it, implementation research has often focused on individual behaviour change without reflecting on, or paying attention to, the characteristics of health technologies, the processes by which health technologies are adopted and sustained, or a workable understanding of the particular context in which implementation occurs [7].

Successive reviews of the evidence for successful translation of research findings into healthcare practice reveal that a range of implementation strategies can be successful. However, why strategies work in some circumstances but not others remains unclear [3,6,8].

Using theory to guide the exploration of the local context for implementation can help [6]. First, relevant theories enable the tailoring of strategies to the most significant barriers to translating research into practice in a given context. Second, theories enable researchers to build on existing knowledge and increase the transferability of findings to settings and contexts other than the immediate research environment [9].

TRiPLaB will use theory to guide its exploration of context in our collaborating healthcare organisations. This exploration will in turn inform the development of tailored implementation strategies for innovation delivery. The synthesis of research findings by Greenhalgh *et al*. [5] on the dissemination and implementation of research-based innovations provides the theoretical framework for TRiPLaB. Their analysis proposes that successful innovation adoption requires analysis of the characteristics of the innovation itself, the perceptions of those individuals tasked with adopting the innovation, and the wider organisational cultures in place in the setting for adoption. Shaped by diffusion of innovation theory [10], Greenhalgh *et al*. also acknowledge the influence of channels of communication, or social networks, between practitioners as important influences on whether, and how quickly, an innovation is adopted. In adopting this particular theoretical framework, TRiPLaB will explore the relative influence of these often overlooked but important elements at individual, team and organisational levels in our NHS partners [2-6]. This theory-informed exploration will form our 'diagnostic analysis' [3] of the local context in each of the NHS healthcare organisations that make up our case study series.

## Methods

Ethical approval for this study was given by York Research Ethics Committee (REC 10/H1311/1).

### The Develop, IMplement, Evaluate (DIME) approach of TRiPLaB

TRiPLaB is a multisite, longitudinal, mixed methods case study. Currently, we are working with NHS Bradford and Airedale (an NHS commissioning and community provider organisation) to translate research-based findings into practice in the areas of maternal mental health and stroke care, and with Leeds Partnership Foundation Trust (a provider of mental health services) to enhance the implementation of recent and relevant NICE guidance.

Each case study will have three sequential phases (see Figure 1): the findings from the development phase (phase one) lead into the implementation phase (phase two), and the outcomes of this are assessed in the evaluation phase (phase three). The three-phase approach has been informed by the Medical Research Council's framework [11] for developing and evaluating complex interventions, acknowledges the need to use theory in planning and analysis, recognises the importance of local context, piloting, and evaluating intervention components, and the use of multiple outcome measures to evaluate intervention effectiveness. The three phases are summarised below.

**Figure 1 F1:**
[figure not shown]
**The Develop, Implement, Evaluate model of TRiPLaB**.

Phase one is a development phase in which the innovation that is the focus of each case study will be selected and its key characteristics mapped. Theory-informed factors hypothesised as influential in health professionals' adoption of the selected innovation into routine practice are explored and mapped.

Phase two is an implementation phase in which tailored behaviour-change interventions are developed piloted and delivered using personnel from TRiPLaB and its partner organisations.

Phase Three is an evaluation phase in which changes in structure, process, and outcome are described and evaluated. We will be looking at change both within and, towards the end of the programme, between case studies.

TRiPLaB will use the resources of the Centre for Reviews and Dissemination (CRD) to increase the accessibility of research evidence to decision makers (particularly commissioners) in the NHS. Primarily, we will do this by using tailored briefings relating research evidence to specific decision problems and context in Bradford and Leeds. These 'evidence briefings' will be based on existing sources of synthesised and quality assessed evidence - for example, CRD's databases of systematic reviews (DARE) and economic evaluations (NHS EED). We will develop and implement methods for producing and disseminating evidence briefings and evaluate their perceived usefulness, costs, and use by decision makers.

### Development phase (phase one)

#### Selecting the innovation

At the start of each case study, the specific innovation to be targeted will be selected. The selection will be based on the results of: a qualitative stakeholder consultation designed to identify key topics; a conjoint analysis survey of commissioners and practitioners designed to explore those characteristics of innovations likely to influence individuals' prioritisation of them; and a mapping exercise exploring how each of the stakeholder short-listed topics 'scores' against the characteristics measured in the conjoint analysis survey (for example, local capacity and expertise for implementation, cost/impact on local budgets). We will also consider pragmatic issues, such as the presence or absence of routine data sources to aid the measurement of innovation adoption.

Stakeholder consultations will focus on identifying key topics in the relevant clinical area. For example, in NHS Bradford and Airedale, stakeholder consultation in the area of child and maternal health care with a range of commissioners and practitioners revealed the importance of maternal mental health as a focus for activity.

The conjoint survey will reveal the characteristics [6] that influence an individual's decision to prioritise one innovation over another. The factors that make up the conjoint profiles to be evaluated will include characteristics such as the strength of supporting evidence base behind an innovation and its economic costs. By conjoint analysing the characteristics of potential innovations, we will be able to 'plug in' future innovations and inform the organisation's understanding the likelihood of successful implementation. This has the obvious advantage of not having to ask the healthcare workforce or consumers to rank or rate innovations on multiple occasions. The conjoint analysis also reduces the likelihood of the TRiPLaB team targeting respondents (for example, as change agents) who may not favour the innovation eventually selected.

The mapping exercise will score short-listed innovations against characteristics measured in the conjoint analysis survey. For example, the strength of supporting evidence base for each of the short listed innovations from the stakeholder consultation will be explored through reference to published systematic reviews. The outcome of this process will be summarised in a matrix. Finally, the pragmatic factors to be considered will include whether suitable process of care and health outcome measures are available through routinely collected data to evaluate the impact of the implementation strategies, or whether tailor-made, repeatable, audits have to be established.

The selected innovation for each case study will be one that has been identified as a key topic from the stakeholder consultation that scores highly on those characteristics identified from the conjoint analysis survey as influential in commissioners' and practitioners' prioritisation of innovations, and can be monitored through tailor-made audits or, preferably, via routinely collected data. In sum, the combination of stakeholder consultation, the conjoint survey of practitioner and commissioner preferences, and the mapping exercise will enable us to select a robust but feasible innovation to target in each case site.

#### Exploring the local context

Following selection of the innovation to be targeted, we will undertake a diagnostic analysis [3] in which we will administer a second survey in each case site to measure health professionals' attitudes towards the innovation, health care team innovation culture (using the Team Climate Inventory [12]), and the social networks/communication channels between health professionals with regards to the innovation. A series of semi-structured interviews will also be conducted with a sample of the health professionals to further explore perceived barriers to implementation, and to gain a richer understanding of the influence of health care teams and social networks in the uptake and adoption of new innovations into practice.

Quantitative survey data will be synthesised using multilevel modelling (MLM) approaches to identify the hierarchical level most likely to be responsive to the implementation strategies developed. For example, if the MLM identifies healthcare team culture to be particularly influential, a multifaceted intervention specifically targeting a team's culture towards innovation might (*a priori*) be more successful than an intervention targeting only individual attitudes towards the innovation. This focus is deliberate given the current dearth of implementation research examining the influence of factors at different hierarchical levels in the health care system, and recommendations for further research in this area [13]. The qualitative data collected from the semi-structured interviews will be analysed using thematic analysis and combined with the outcome of the MLM to gain a richer understanding of the local context and to help tailor the implementation strategies.

### Implementation phase (phase two)

Development of the intervention will be systematic, specifying intervention objectives, developing specific implementation strategies to satisfy these objectives, and piloting strategies to assess their likely impact and test how they will be received by the health professionals. This piloting and modelling prior to rolling out implementation strategies/behaviour-change interventions is a necessary prerequisite stage [11]. The objectives and design of the intervention will be determined by the outcome of the development phase, in particular the results of the planned multilevel modelling. The selection and design of the actual intervention components will be informed by existing systematic, and other, reviews of the relevant literature.

Having decided on the innovation in phase one and possible implementation strategies in phase two, we will make the final choice on our implementation approach with reference to the idea of 'policy' cost effectiveness [14]. Summary data on: the innovation from Phase One (net cost per patient and likely health gain per patient); the implementation strategies under consideration (net cost of planned implementation and likely change in adoption/adherence); and local scale factors (for example, the number of NHS organisational units involved and number of patients targeted) will be combined to arrive at a policy cost effectiveness figure for each option. The combination with the highest cost effectiveness will be the option pursued.

The failure to adequately describe interventions in the context of research and the commensurate reduction in others' ability to then use successful programs -- or conversely, avoid making the same mistakes as unsuccessful ones -- is common in healthcare research [15]. For each of the case studies in the TRiPLaB program we will describe: the intervention and its component parts in sufficient detail that others could reproduce it; why the specific intervention was chosen; and a fidelity measure of how well the intervention was delivered. For example, if we undertake educational outreach or training as a component of an intervention, we will detail how many sessions each unit of analysis receive, and when and where the training took place.

### Evaluation phase (phase three)

Following the recommendation to conduct exploratory trials prior to embarking on more definitive randomised controlled trials [11], TRiPLaB will employ three different methods to evaluate the impact of the tailored implementation strategies delivered in each case study. The findings from these evaluation measures will inform (if worthwhile) later randomised controlled trials. The three methods to be used are: interrupted time series analysis of either tailor-made audit data or routinely collected data to estimate the impact of the intervention upon suitable process of care and outcome measures; comparison of pre- and post-intervention scores of survey-gathered measures of individual attitudes, team culture, and changing nature, composition, and size of social networks; and a qualitative process evaluation of why the intervention worked (or did not work).

Alongside these three primary evaluation methods we will also collect cost data on the resources used in the delivery of implementation approaches. The micro costs [16] associated with each strategy will be estimated alongside the extent of behavioural change achieved to arrive at summary estimates of implementation cost effectiveness [14] for each of the case studies in the programme.

### Interrupted time series analysis

Interrupted time series designs compare multiple 'before and after' (the introduction of a change strategy) measures to detect whether an intervention has had an effect over and above any underlying trend in the data [17]. Time series analysis has been used as a technique for evaluating the effectiveness of health care interventions [18]. In the case studies, routinely collected process (health professionals' adoption of the innovation) and health outcome measures (dependent on the innovation selected) will provide the multiple time points necessary to perform a time series analysis. Time, possible seasonal trend, and possible upward trend, commonly occurring following the introduction of a new innovation [10], will be modelled into the analysis. This will be the primary outcome measure for each case study.

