### Qualitative process evaluation

Qualitative interviews with health professionals receiving the intervention will enable an exploration of their perceptions of what worked and what did not work in the intervention, providing insight into the 'black box' of intervention effectiveness [19]. In combination with the measure of fidelity taken during the implementation phase, these qualitative interviews comprise a process evaluation of the intervention, addressing recommendations to monitor intervention delivery and receipt by participants [11,20]. The data will be analysed using a framework approach [21]: familiarisation with the data, identification of a thematic framework, indexing, charting, and finally, mapping and interpretation with reference to the overall aim of TRiPLaB as well as the themes revealed by the data.

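### Where the adoption indicator depends on documentation by the targeted professionals, the uncontrolled time series cannot tell better recording from launch apart from real adoption

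*Protocol article*

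**What the plan says.** Four parts of the protocol article bear on this.

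- **Endpoint.** The section on interrupted time series analysis takes its data from "routinely collected process (health professionals' adoption of the innovation) and health outcome measures (dependent on the innovation selected"). Of this analysis it says: "This will be the primary outcome measure for each case study". The evaluation phase section widens the source to "interrupted time series analysis of either tailor-made audit data or routinely collected data".
- **Choice of indicator.** In the section on selecting the innovation, the chosen innovation must be one that "can be monitored through tailor-made audits or, preferably, via routinely collected data". The same section asks that measures be suitable and audits repeatable. It does not mention whether the record is independent of the staff being targeted.
- **Model.** "Time, possible seasonal trend, and possible upward trend, commonly occurring following the introduction of a new innovation [10], will be modelled into the analysis". No control or comparison series is described there. The abstract lists "Mixed research methods, including time series analysis, quasi-experimental comparison, and qualitative process evaluation" but does not tie the comparison to the time series.
- **Who is targeted and who delivers.** The process evaluation refers to "Qualitative interviews with health professionals receiving the intervention", so the strategy's recipients are the people whose adoption is the process measure. In the phase summary below Figure 1, "tailored behaviour-change interventions are developed piloted and delivered using personnel from TRiPLaB and its partner organisations".

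The article does not state who enters the routine records or who abstracts the audits.

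**The concern.** A strategy that draws professionals' attention to one innovation may lead them to use it more, to write it down more reliably, or both. If the process indicator counts documented use, both changes raise it, and both begin at launch. An interrupted time series without a control attributes a change at the break, beyond the modelled trend and season, to the intervention. A change in measurement at the break is therefore a direct threat to its interpretation.

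The settings named in the article are maternal mental health, stroke care and uptake of NICE guidance. Process measures there may well depend on clinicians noting what they did.

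The adoption estimate also matters beyond its own test. The evaluation phase section combines the extent of behavioural change with micro-costs to give implementation cost-effectiveness, and uses the findings to decide whether later randomised trials are worthwhile. A spurious step would flatter both.

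**Working it through.** The article gives no effect size, number of time points, alpha or power, so there is no figure of the plan's to reproduce. The check has three parts. All numerical inputs are assumptions.

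**1. What the series can identify.** Let *a* be true adoption and *c* the completeness of recording, with subscript 0 before launch and 1 after. Assume that no use is recorded falsely. Then:

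- recorded adoption = *a* × *c*
- step at launch = *a*₁*c*₁ − *a*₀*c*₀ = *c*₀(*a*₁ − *a*₀) + *a*₁(*c*₁ − *c*₀)

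The first term is real change as seen through the record; the second is recording change. The series shows only their sum. Terms for time, season and trend describe how the product moves and cannot split it.

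**2. Size of the false step when true adoption does not change.** Here the step is *a* × (*c*₁ − *c*₀). For *a* = 40%:

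- 80% to 90%: 0.40 × 0.80 = 0.32; 0.40 × 0.90 = 0.36; step = 0.04, or 4 points.
- 70% to 90%: 0.40 × 0.70 = 0.28; 0.40 × 0.90 = 0.36; step = 0.08, or 8 points (0.08 / 0.28 = 29% relative).

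Over a wider range of true adoption, the false step in percentage points is:

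| Completeness before → after | *a* = 30% | *a* = 50% | *a* = 70% |
|---|---|---|---|
| 80% → 80% | 0 | 0 | 0 |
| 80% → 85% | 1.5 | 2.5 | 3.5 |
| 80% → 90% | 3 | 5 | 7 |
| 70% → 90% | 6 | 10 | 14 |

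**3. Effect on the test of the level change.** A segmented ordinary least squares regression (time, level change, slope change) was simulated 3,000 times per scenario. Each series had 24 monthly points, 12 before and 12 after launch, with 100 records per point. True adoption was constant at 50%, with no seasonality or autocorrelation.

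| Completeness before → after | Mean estimated step (points) | Rejected at 5% |
|---|---|---|
| 80% → 80% | 0.0 | 5.1% |
| 80% → 85% | 2.5 | 10.1% |
| 80% → 90% | 5.1 | 23.2% |

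With stable recording the test holds its level. With a recording jump at launch, the mean estimate equals the calculated false step to within simulation error, and false rejection rises about twofold (10.1 / 5.1) and four- to fivefold (23.2 / 5.1). The time and slope terms in the model do not absorb the jump.

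**Do other parts of the plan catch it?** The fidelity measure concerns delivery of the intervention. The before-and-after surveys measure attitudes, team culture and networks, which could improve alongside documentation. The interviews collect views on what worked. None of them checks the adoption records.

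**The case against.** The strongest reply is that the point rests on silence. This is a condensed programme article: the innovation, data source and measures are chosen separately for each case study in phase one, and who records or abstracts may be set out in a fuller document not shown. That reply stands as far as it goes. Missing abstraction detail alone would be no finding. What the article itself sets is the preference among data sources and the terms of the primary model, and neither deals with recording.

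A reader might infer more than the text supports:

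- **That targeted staff make the records, or that deliverers abstract the audits.** The article says neither. Partner personnel are named only as helping to develop, pilot and deliver the strategy.
- **That the mere existence of a source is the only data condition.** Suitability of the measures and repeatability of the audits are also asked for, though neither addresses who records.
- **That the bias always favours the intervention.** It does so for an indicator that counts recorded use when recording becomes more complete. Clearer definitions could reduce over-recording, and better recording of health problems could make outcomes look worse.
- **That a process step alone would lead to a declaration of effectiveness.** The article states no success rule, calls the work exploratory, and includes health outcome measures that need not move with documentation.

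The abstract's quasi-experimental comparison could become a safeguard, but the time series section does not describe it as a control. A comparison series also has a limit: an untargeted item need not move when attention is confined to the targeted one, so a flat series gives only partial reassurance.

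**Conclusion.** The point holds as a conditional risk. The process part of the primary outcome is recorded adoption, analysed in a series with no described control. If the chosen indicator depends on documentation by the targeted professionals, and if recording improves from launch, the described model cannot distinguish that from real adoption.

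With true use constant at 40%, the false step is 4 points for completeness rising from 80% to 90% and 8 points for 70% to 90%. Across true use of 30% to 70% and the three completeness rises tabulated, it runs from 1.5 to 14 points. These figures illustrate the mechanism and do not forecast any case study. The rejection rates also depend on the assumed length and size of the series.

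The documents do not support saying that the primary result will be biased, or that every case study is exposed. An indicator generated independently of the targeted staff would largely avoid the problem, and health outcome measures may be less exposed. The point merits action because the indicator is selected in phase one, and a safeguard is easier to build in then than to recover at analysis.

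**What to change.** 1. **Selecting the innovation.** Add a tie-break: among otherwise suitable indicators, prefer one that the targeted professionals do not themselves complete. This should remain a preference, since an absolute rule could override the stakeholder and conjoint results that drive selection.
2. **Interrupted time series analysis.** Where the indicator is self-recorded, add a comparison series: the recording of an untargeted item from the same record system over the same period, analysed with the same model. Use it as a sensitivity check on the adoption step. Do not subtract its step, because that would assume equal recording shifts across items. State that it detects a general change in recording but not one specific to the targeted item.
3. **Tailor-made audits.** Use the same form before and after launch, abstracted by existing staff who do not deliver the strategy.

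The cost is one extra series to analyse and some allocation of tasks among existing staff. The downside is that some convenient indicators become second choice.
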